# Thermographic evaluation of acupoints in lower limb region of individuals with osteoarthritis: A cross-sectional case-control study protocol

**DOI:** 10.1371/journal.pone.0284381

**Published:** 2023-04-14

## Abstract

**Purpose:**

Acupuncture has been widely used in the treatment of knee osteoarthritis (KOA), but the selection of acupoints is indeterminate and lacks biological basis. The skin temperature of acupoints can reflect the state of local tissue and may be a potential factor for guiding acupoint selection. This study aims to compare the skin temperature of acupoints between KOA patients and the healthy population.

**Study design and methods:**

This is a protocol for a cross-sectional case-control study with 170 KOA patients and 170 age- and gender-matched healthy individuals. Diagnosed patients aged 45 to 70 will be recruited in the KOA group. Participants in the healthy group will be matched with the KOA group based on mean age and gender distribution. Skin temperature of 11 acupoints (ST35, EX-LE5, GB33, GB34, EX-LE2, ST34, ST36, GB39, BL40, SP9, SP10) will be extracted from infrared thermography (IRT) images of the lower limbs. Other measurements will include demographic data (gender, age, ethnicity, education, height, weight, BMI) and disease-related data (numerical rating scale, pain sites, duration of pain, pain descriptors, pain activities).

**Discussion:**

The results of this study will provide biological evidence for acupoint selection. This study is a precondition for follow-up studies, in which the value of optimized acupoint selection will be verified.

**Trial registration:**

ChiCTR2200058867.

## Introduction

Knee osteoarthritis (KOA) is one of the most common musculoskeletal diseases and an important cause of chronic pain and lower limb disability among elderly individuals [1]. As one of the most popular nonpharmacologic therapies, acupuncture has long been used in the treatment of KOA in many countries. The Osteoarthritis Research Society International (OARSI) guidelines [2] and the American College of Rheumatology (ACR) guidelines [3] recommend acupuncture conditionally, while the National Institute for Health and Care Excellence (NICE) [4] does not recommend acupuncture. There have been inconsistent results in studies using acupuncture; researchers have proposed potential reasons for these inconsistencies, including the selection of acupoints, dosage, and the rationality of the sham acupuncture design [5]. Acupoint selection is a central component in clinical operation as well as a report standard [6]. In high-quality KOA studies, two acupoint selection methods were commonly used. One is composed of fixed acupoints (meaning that all participants in the acupuncture group were used) and optional acupoints [7, 8]. The other one only contained optional acupoints [9–11], that is, a certain number of acupoints was selected from them. Regardless of which method is adopted, acupoint selection varies greatly among studies. At present, the selection of acupoints mainly depends on traditional acupuncture theory and doctors’ clinical experience; this lack of a specific biological basis leads to different selections. According to research reports [12, 13], more than 40 acupoints can be used for KOA. However, little evidence is available about how many of these acupoints actually take effect, or which ones are more effective.

Some sensitizations can be found on the body surface of KOA patients, such as pain sensitization and thermal alteration. These sensitizations can guide both diagnosis and treatment [14, 15]. Acupoints also have the characteristics of sensitization. The biological characteristics of acupoints (such as skin temperature [16], tenderness threshold [17], and morphology [18]) may change in pathological conditions. Acupoints are specific points on the body surface, and sensitizations of a certain area should be similar to those of acupoints within this area, which provides a basis for acupuncture therapy. As a typical example, acupoint selection of dry needling can be guided by trigger points [19]. However, these links to skin temperature have not been explored clearly. Most acupoint selection methods guided by sensitization phenomena have large individual differences, with difficulties expanding. As a little-attention part of sensitization, skin temperature may be a more universal and objective factor to guide acupoint selection.

Infrared thermography (IRT) is a technology that collects focal plane temperature information within the field of view and displays surface temperature distribution in pseudocolor form [20]. IRT has high temperature sensitivity, which can reflect blood circulation and metabolism of tissue to be applied in medicine as a diagnostic test or outcome measurement [21]. Some abnormal skin temperature areas can be found in patients with KOA or other osteoarthritis [22, 23]. Recent evidence suggests that thermal alteration can reflect the progress of KOA and guide medical practice [15]. However, there is insufficient evidence to link these sensitized areas to acupoints. To further understand the characteristics of acupoints under pathological conditions, this cross-sectional case-control study will explore special manifestations of skin temperature of acupoints in patients with KOA by IRT. The results of the study will provide a theoretical basis for further optimizing the selection of acupoints.

## Objectives

### Primary objective

The primary objective of this study is to investigate the difference in the skin temperature of acupoints between KOA and healthy populations.

### Secondary objectives

The secondary objective of this study is to explore the influence of gender, painful area and pain level on the skin temperature of acupoints in KOA patients.

## Methods

### Study design

This will be a cross-sectional case-control study conducted in Beijing, China. A total of 340 participants (170 KOA patients and 170 healthy individuals) will be recruited in Dongzhimen Hospital Affiliated to Beijing University of Chinese Medicine, Jiaodong Community Health Service Station, Xiaoguan East Street Community Health Service Station and Deluyuan Community Health Service Station. This study was approved by the ethics committee of Beijing University of Chinese Medicine (No. 2022BZYLL0304). The protocol (version number: V1.2, 2022/04/18) has been registered on the Chinese Clinical Trial Registry (ChiCTR) (registration number: ChiCTR2200058867). Written informed consent will be obtained from all participants before recruiting. Study results will be disseminated in peer-reviewed publications. This study will follow the Strengthening the Reporting of Observational Studies in Epidemiology (STROBE) [24] statement. Although this is an observational study, an adjusted SPIRIT schedule can be found in Fig 1 which clearly shows the overview of this study.

**Fig 1 pone.0284381.g001:**
[figure not shown]
SPIRIT schedule.

### Participants

Patients with KOA and age- and gender-matched healthy control individuals will be recruited in hospital and health service stations through doctors’ recommendations and print advertisements. Participants will be initially screened to determine if they meet the criteria. After signing the informed consent, eligible participants will be asked to complete a series of questionnaires and undergo an IRT examination.

### Inclusion criteria

The inclusion criteria for the KOA group are as follow: (1) meet the ACR clinical diagnostic criteria [25] of KOA; (2) aged 45–70 years old; (3) have unilateral/bilateral knee pain for more than 6 months; (4) have X-ray examination showed Kellgren-Lawrence grade [26] Ⅱ or higher within 6 months; (5) score 4 or high in numerical rating scale (NRS) during the past week for knee pain; (6) sign the informed consent.

The inclusion criteria for the healthy control group are as follow: (1) without knee pain in the past year; (2) aged 45–70 years old; (3) signed informed consent.

### Exclusion criteria

The exclusion criteria include (1) history of knee surgery; (2) knee pain caused by other diseases (such as severe effusion in the joint cavity, infection, malignant tumor, autoimmune disease, trauma, fracture, gout, lumbosacral disease, or rheumatic arthritis); (3) severe acute/chronic organic or psychoneurological diseases (such as epilepsy or severe anxiety/depression); (4) received drug therapy (such as nonsteroidal anti-inflammatory drugs or opioids) or nonpharmacologic therapy (such as acupuncture, moxibustion, infrared physiotherapy, or tuina) or any other treatment that may affect skin temperature distribution in the lower extremities during the past 2 weeks; (5) varicose veins, deep vein thrombosis, skin inflammation, allergic reactions or other factors that may affect the skin temperature distribution in the lower extremities; and (6) wearing excessive warm clothing or protective gear on the lower extremities for the past 24 hours.

### IRT measurement

#### Measuring locations

The skin temperature of 11 acupoints most commonly used for KOA will be measured [12]. The most commonly used acupoints include *dubi* (ST35), *neixiyan* (EX-LE5), *xiyangguan* (GB33), *yanglingquan* (GB34), *heding* (EX-LE2), *liangqiu* (ST34), *zusanli* (ST36), *xuanzhong* (GB39), *weizhong* (BL40), *yinlingquan* (SP9), and *xuehai* (SP10). The positioning of acupoints is shown in Table 1, which follows WHO Standard Acupuncture Locations.

**Table 1 pone.0284381.t001:** Positioning of acupoints.

Acupoint	Location
*Dubi* (ST35)	On the anterior aspect of the knee, in the depression lateral to the patellar ligament
*Neixiyan* (EX-LE5)	On the anterior aspect of the knee, in the depression medial to the patellar ligament
*Xiyangguan* (GB33)	On the lateral aspect of the knee, in the depression between the biceps femoris tendon and the iliotibial band, posterior and proximal to the lateral epicondyle of the femur
*Yanglingquan* (GB34)	On the fibular aspect of the leg, in the depression anterior and distal to the head of the fibula
*Heding* (EX-LE2)	On the anterior aspect of the thigh, in the depression superior to the base of the patella
*Liangqiu* (ST34)	On the anterolateral aspect of the thigh, between the vastus lateralis muscle and the lateral border of the rectus femoris tendon, 2 cun ^a^ superior to the base of the patella
*Zusanli* (ST36)	3 cun directly below ST35, and one finger-breadth lateral to the anterior border of the tibia
*Xuanzhong* (GB39)	On the fibular aspect of the leg, anterior to the fibula, 3 cun proximal to the prominence of the lateral malleolus
*Weizhong* (BL40)	On the posterior aspect of the knee, at the midpoint of the popliteal crease
*Yinlingquan* (SP9)	On the tibial aspect of the leg, in the depression between the inferior border of the medial condyle of the tibia and the medial border of the tibia
*Xuehai* (SP10)	On the anteromedial aspect of the thigh, on the bulge of the vastus medialis muscle, 2 cun superior to the medial end of the base of the patella

^a^ 1 cun (≈20 mm) is defined as the width of the interphalangeal joint of patient’s thumb.

#### IRT data acquisition specification

To ensure the standardization of data collection, data collection specifications referred to the Delphi study and consensus statement on the measurement of human skin temperature [27]. Similar specifications was reported in our previous study [28]. Specific specifications are as follows:

Personal information of all participants will be recorded in data sheets.Participants will not be allowed to consume alcohol within 4 hours before the measurement.Participants will not be allowed to conduct vigorous exercise, or to events that may severely interfere with skin temperature, such as electrotherapy, ultrasound, heat or cold exposure within two hours prior to measurement.The ambient temperature will be controlled at 25±2°C, and the relative humidity of the air will be controlled at 40%-50%.In the field angle of the infrared thermal image, there will be no interference heat source and obvious air flow.The IRT detection equipment will be a TMI-M (Beijing Wholelife Medical Science Co., Ltd) portable medical infrared thermal imager. The thermal sensitivity is 0.05°C at 30°C, the spectral range is 7.5–13 μm, the image pixel size is 256×336, and the acquisition frequency is 25 Hz.To make the equipment work in a steady state, the infrared thermal imager will be powered 0.5 hours before data collection.The vertical distance between the participants and the camera will be 1.5 meters.The centerline of the lens field angle will be perpendicular to the human body by a liftable gimbal.The emissivity of the detector will be 0.98 (default value).The image collection time for all participants will be 9:00–16:00.All participants will stay in the same posture, as shown in Fig 2.The IRT image data processing software was independently developed by the study team. This software has been verified to be reliable and maintains all original data characteristics. The data file contains temperature values of any spatial coordinates in all field angles. The data file is filled in a 16-bit integer data format and stored in *.dat.

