### Data correction and statistical analysis

#### Correction of skin temperature

Human skin temperature is individual and affected by basal body temperature [30]. A previous study [31] showed that relative temperature, which can control bias from individual differences, is more valuable than absolute temperature under specific conditions. Relative temperature can eliminate the systematic error caused by factors such as body and ambient temperature, and truly express the temperature characteristics in the ROI. Using the quantification method of relative temperature, the temperature value in the ROI will be subtracted from the temperature value of other regions (reference areas) specified in the same image. In this study, at the same time that the absolute temperature will be reported, relative temperature will be analyzed as the main indicator. The specific correction formula for relative temperature is as follows:

$$T_{c}=T-\bar{T}$$

*T_c_* is the measured value of the skin temperature of the acupoint after correction. *T* is the absolute skin temperature of the acupoint (the actual value measured). $\bar{T}$ is the control temperature, means the average skin temperature of the corresponding reference area. As shown in Fig 4, the reference area is the entire lower limb region on the IRT image which used to locate the acupoint.

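### Cases and controls are not balanced or adjusted for imaging time, site or room temperature, and subtracting the limb mean removes only shifts that are uniform over the limb

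*Protocol article*

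**What the plan says.** The relevant statements in the Protocol article are these.

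- **Imaging time** (IRT data acquisition specification): "The image collection time for all participants will be 9:00–16:00". This is a 7-hour window with no rule for how the groups are spread within it.
- **Room** (same section): "The ambient temperature will be controlled at 25±2°C", a span of 4 °C. Humidity, air flow, posture, alcohol, vigorous exercise and heat or cold exposure are also restricted.
- **Matching** (abstract): "Participants in the healthy group will be matched with the KOA group based on mean age and gender distribution". The Participants section likewise names only age and gender.
- **Sites** (Study design): one hospital and three community health service stations. No rule ties both groups to the same site or period.
- **Correction** (Correction of skin temperature): the primary outcome is acupoint temperature minus the mean of a reference area, where "the reference area is the entire lower limb region on the IRT image which used to locate the acupoint". The stated reason is that "Relative temperature can eliminate the systematic error caused by factors such as body and ambient temperature".
- **Analysis** (Statistical analysis): a two-group test without covariates. The exploratory regression lists age, gender, BMI, pain site and NRS, with no term for time, room temperature or site.
- **Outcomes** (Disease-related data): relative temperature at 11 acupoints is primary. Absolute temperature at the same points is secondary.

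**The concern.** A window that applies to everyone limits the range of conditions. It does not make the two groups alike within that range. If cases and controls differ in their mix of time slots, sites or room temperatures, and skin temperature responds to these, the group comparison contains that response as well as any disease effect. Nothing in the stated matching, test or covariates would separate the two.

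Absolute temperature has no correction, so such an imbalance enters it in full. For relative temperature the claim of elimination goes too far, because one subtracted mean cannot remove a change in the pattern of temperature over the limb. The article treats changes of distribution as real: its exclusion criteria remove people with recent treatments or conditions that may alter the distribution of skin temperature in the legs.

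Acupoint-specific group differences are the main result and are meant to support a later randomized trial of acupoint selection. A Bonferroni threshold, a larger sample and blinded analysts do not protect against bias of this kind.

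**Working it through.** **1. The plan's own figure.** Inputs from Sample size calculation: means 0.11 and −0.23 °C, so the difference is 0.34 °C; SD 0.79 °C in each group; two-sided α = 0.0045; power 80%.

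Normal approximation: n = 2 × [0.79 × (z for α/2 + z for 80%) / 0.34]² = 146.4, so 147 per group. The two-sample t calculation gives 149 per group (power 80.2%). The stated 149 is reproduced, read as per group.

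**2. What the subtraction does.** Suppose conditions move the whole limb by s and the acupoint by a further r relative to the limb mean. Then

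T_c = (T + s + r) − (T̄ + s) = (T − T̄) + r.

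The uniform part s cancels and r stays. If the mean of r differs between groups by b, the comparison of relative temperature is biased by b. In absolute temperature both s and r remain.

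**3. From imbalance to bias.** If relative temperature at a point differs by x °C between two slots, and the groups differ by a share d in how often they fall in one slot, then b = x × d. Neither x nor d is in the documents, so both are assumptions:

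- x = 0.1, d = 0.2: b = 0.02 °C
- x = 0.25, d = 0.2: b = 0.05 °C
- x = 0.5, d = 0.2: b = 0.10 °C
- x = 0.5, d = 0.4: b = 0.20 °C

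**4. Effect on the error rate.** I take the stated SD for every acupoint. SE = 0.79 × √(2/149) = 0.0915 °C and the critical z is 2.841, so an observed difference of about 2.841 × 0.0915 = 0.26 °C is significant. With no disease effect,

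P(significant) = Φ(b/SE − 2.841) + Φ(−b/SE − 2.841).

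| Residual bias b (°C) | b as share of 0.34 °C | False-positive rate per acupoint |
|---|---|---|
| 0 | 0% | 0.0045 |
| 0.02 | 6% | 0.0055 |
| 0.05 | 15% | 0.011 |
| 0.10 | 29% | 0.040 |
| 0.20 | 59% | 0.26 |

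Example for b = 0.10: b/SE = 1.093, and Φ(−1.748) + Φ(−3.934) = 0.040.

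No such rate can be given for absolute temperature, because the article states no SD for it.

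**The case against.** The strongest reply is that the primary outcome is built to deal with this. Any limb-wide shift from the room, the body or the time of day cancels within the image. The article also limits what could disturb the pattern: no vigorous exercise or heat or cold exposure for two hours, no alcohol for four, controlled humidity, no obvious air flow, a fixed posture, and exclusion of people recently in very warm clothing. The acquisition rules are said to draw on a Delphi consensus. Both groups share one recruitment route: "Patients with KOA and age- and gender-matched healthy control individuals will be recruited in hospital and health service stations through doctors’ recommendations and print advertisements". The article also condenses a fuller protocol and refers to operating procedures and case report forms, where scheduling and the recording of time and room temperature may be set out.

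Much of this stands. It confines the problem for the primary outcome to non-uniform change and makes a large residual bias less likely. It does not balance the groups, and it leaves absolute temperature uncorrected. The unadjusted comparison, the matching variables and the claim of elimination are stated, so the point does not rest on silence alone.

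A reader might go further and infer that imaging runs through all seasons, that controls are added late to fit the case profile, that patients come in clinic hours and volunteers at other times, or that proximal and distal points would be biased in opposite directions. The documents support none of this. No recruitment dates or separate schedules are given, and of the 11 points in Table 1 only GB39 lies near the ankle.

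**Conclusion.** The point holds as a minor one. The article neither balances nor adjusts for imaging slot, site or room temperature, and it credits the limb-mean subtraction with more than it can do. Absolute temperature is exposed directly. Relative temperature is exposed only to a non-uniform change that differs between groups.

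The size is unknown. Under the assumed biases of 0.02 to 0.20 °C the per-acupoint false-positive rate runs from about 0.0055 to 0.26, against 0.0045 planned, and it stays at 0.0045 if the change is uniform or the groups are balanced. The upper figure should not be read as the expected error rate. In the example above it needs a 0.5 °C change in temperature that has already been corrected, which is more than the whole planned difference of 0.34 °C, together with a 40-point imbalance in slots. The documents show neither.

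**What to change.** 1. Image cases and controls concurrently at each site, and balance them on morning and afternoon slots.
2. Record clock time, date and room temperature for every image, if the case report form does not already do so.
3. At the existing data check (every 20 participants or after one month, under Quality control), compare the groups on site, slot and room temperature, and book the next participants to restore balance.
4. Add site, time and room temperature as covariates in the comparison of absolute temperature, and in a sensitivity comparison for relative temperature. The planned primary test can stay as it is.
5. In Correction of skin temperature, say that the subtraction removes shifts uniform over the limb, in place of the claim that it eliminates body and ambient error.

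The cost is slightly less flexible booking and three recorded fields. The sample size and the participants' procedures do not change. Steps 1 to 3 must be in place before imaging, since conditions that were not recorded cannot be adjusted for later.

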**Fig 2 pone.0284381.g002:**
[figure not shown]
Standing posture of participants.

### Extraction method for skin temperature of acupoints

After obtaining the IRT image, a region of interest (ROI) will be drawn to extract the skin temperature of the acupoint. The IRT image contains both lower limbs. For the KOA group, the side with more severe symptoms will be used as the evaluation side. For the healthy control group, one side will be randomly selected for evaluation.The size of the ROI is a circular area with a radius of 3 pixels centered on the acupoint positioning (fixed by software). The location of the ROI is shown in Fig 3.The average value of the temperature will be extracted from the ROI; the value will be rounded up to 2 decimal places.The ROI region will be drawn on the IRT images by 2 researchers independently. When the skin temperature of the acupoint is inconsistent, a third researcher will assist in discussing the ROI location.IRT images can be presented in greyscale or pseudocolor. Since the pseudocolor image will weaken landmarks on the image, which will affect acupoint positioning, all ROI regions will be drawn on greyscale images.

